### Eligibility criteria and processes

All eligible women booking for pregnancy care at the Women’s during the recruitment period will be included in the study. Inclusion criteria include primiparous women with adequate English-speaking ability (i.e. do not require an interpreter) and at ≤30 weeks gestation at first pregnancy booking appointment. Women will also be included if they had a previous stillbirth and no living children. The rationale for recruiting only primiparous women is that the information needs for first time parents are likely to be different than for parents who have already had a child.

To determine eligibility of women, prior to each randomised clinic day, the project coordinator or PhD student will screen all new booking histories to identify eligible women using the GP referral sheet, or available past history (Fig. 1). If identified as eligible, they are considered to be participants in the trial, in either the standard care or intervention arms as per the clinic randomisation schedule. Details of women who are identified as eligible (in either the intervention or standard care arms) will be entered into a password protected database with their estimated due date. These details will be used to facilitate the later checking of birth outcomes, mail-out of surveys and follow up phone calls at the specified data collection time points (described later). Births will be checked 2 weeks after the due date to ensure, as far as possible, that follow up contact occurs only with women who are discharged home with a live baby. The hospital’s electronic data systems will be used to facilitate this process.

**Fig. 1 Fig1:**
[figure not shown]
Recruitment of women to the trial arms. ^a^ Did not attend

### Description of standard care

Women in the standard care arm of the trial will receive the standard information resource at the Women’s, a booklet titled ‘*Having your Baby at the Women’s’*. This booklet includes information about care options at the Women’s and services and support provided during pregnancy and birth at the Women’s. It also includes information on how women should take care of themselves during pregnancy, information about different stages of pregnancy and relevant tests and screening as well as information for women to get ready for labour and birth. Care will be delivered in the usual way using standard resources, and these women will be followed up in order to provide a comparison group.

### Implementation of intervention

On the intervention clinic days, all eligible women will receive the *Growing Together* kit at their first booking visit. The kits will be attached to eligible women’s histories prior to clinic commencing, and will be provided by the midwives doing the booking visit. The research midwife will attend the clinic to ensure that the midwives responsible for the booking visits understand how to provide women with the kit. The research team will provide education about the RCT and the importance of providing the kit only on clinic days randomised to the intervention arm. No kits will be available or accessible outside of the intervention days.

Women who receive a kit will have a sticker added to the alert sheet in their medical record so that staff can continue to use and actively deliver the contents of the kit during subsequent pregnancy visits and beyond. It also means clinicians will know to ask about any concerns or questions in relation to the kit. Women having some pregnancy care with their GPs (referred to as *shared care*) will also have a sticker on their Victorian Maternity Record (VMR) documentation, which is the hand-held medical record that women carry with them to all their pregnancy visits. In addition, a letter explaining the *Growing Together* evaluation will be sent to GPs providing shared care with the Women’s Hospital.

During the RCT, the ‘App’ will be available only to women and their partners randomised to the intervention group. They will be mailed a brief reminder and instructions on how to download the App 1 week after the booking appointment. They will also be sent a letter and a sticker 1 week after birth, with instructions to add the sticker to the Child Health Record book and give the letter (explaining the *Growing Together* evaluation) to their Maternal and Child Health nurse (MCHN). The Women’s Hospital will also send out a letter explaining the *Growing Together* kit to the main local government area (LGAs) in the Women’s catchment area to be distributed to their MCHNs.

### Study outcomes

The study will evaluate a number of parenting related outcomes (Table 1), all to be compared by trial arm. The outcomes will be:Experience of motherhood.The experience of motherhood questionnaire (EMQ), a 20-item self-report measure [18] will be used as the primary outcome. The EMQ has been described as a coherent and valid measure of overall coping which is significantly related to and indicative of maternal depression, toddler temperament, social support and life events [18]. The EMQ scale scores range from 20 to 80, with lower scores indicating better maternal health and wellbeing.Parental health and emotional wellbeing.The Edinburgh Postnatal Depression Scale (EPDS) and Kessler 6 (K6) will be included in the survey to explore women’s and their partner’s emotional health and wellbeing. The EPDS is a 10-item self-report instrument [19]. Each item has four response options, scored from 0 to 3, with a total score between 0 and 30. The EPDS identifies women and partners likely to be experiencing postnatal depression, with scores ≥10 and > 12 indicating minor and major depression, respectively. K6 is a 6-item screening tool designed to identify emotional distress [20]. Items are rated on a five-point scales, ranging between 0 and 24. A score of ≥8 indicates non-specific distress and psychological symptoms, including depression and anxiety [21].Health-seeking behaviour for baby’s or mother’s own wellbeing.Developmental, emotional and physical health of babies (including infant feeding and infant temperament – sleeping, crying, settling) from birth to 12 months.To measure the baby’s temperament, four items relating to settling the baby (e.g. soothing) and the baby’s behaviour (e.g. crying) will be used. Each item scores from 1 to 3, with scores being averaged across four items [22]. Higher scores indicate more difficulties in settling and managing the baby.Parents’ knowledge and confidence.Parents’ confidence in conducting tasks related to caring for a baby will be measured using four items [23]. Scores to each item range from 1 to 10 which are summed and averaged to give a total score ranging from 1 to 10, with higher scores indicating greater confidence.Parental behaviour and parent-child interaction.Parent-child interactions will be assessed using four parenting dimensions, measuring ‘parenting self-efficacy’, ‘parental responsiveness/warmth’, ‘irritable parenting’ and ‘activities with child’ [22]. These measures were adapted for use in large scale surveys of Australian parents and demonstrated appropriate internal consistency, structural and predictive validity [23, 24], and sensitivity to the effects of parenting interventions [22].

**Table 1 Tab1:** Data collection for the evaluation

	2 month survey	6 month interview	Partner survey	12 month survey
Views of the care and information received during pregnancy, birth and postnatal	X	X	X	
Views and experiences of the Growing Together kit (intervention)	X	X	X	X
Experience of motherhood – EMQ [18]		X		
Parental emotional wellbeing - EPDS [19] & K6 [20]	X	X	X	X
Health-seeking for baby’s or mother’s wellbeing		X		
Developmental, emotional and physical health of infant (e.g. infant feeding; infant sleeping; infant temperament [21])		X		X
Parents’ knowledge and confidence [22]		X	X	X
Parenting behaviour and parent-child interactions [21, 23]		X	X	X

‘Parenting self-efficacy’ will be measured using a single item global rating of the parent’s perception of themselves as being a ‘good’ parent, ranging from ‘1’ being a ‘not very good’ parent to ‘5’ being a ‘very good’ parent [22].

‘Parental responsiveness/warmth’ will be measured using six items from the Child Rearing Questionnaire [25] (scoring from 1 to 5), assessing parents’ expression of warmth, affection and enjoyment with the child [23]. ‘Irritable parenting’ will be measured using five items from Parental Perceptions and Behaviours Scale [26] (scoring from 1 to 5) about frequency of parental anger and irritability toward the child [23].

For these measures, item scores will be summed and then averaged making a total score ranging from 1 to 5 with higher scores indicating higher levels of responsiveness and irritability. Previous research reports internal consistency coefficients of .86 and .87 respectively when used with Australia mothers of infants and young children [21]. ‘Activities with child’ measures the extent to which parents engage in activities with their baby which are likely to support baby development. This will be assessed with four items, asking the frequency of activities with a baby in a typical week, rated on a 4-point scale from 1=‘not at all’ to 4 = ‘every day’ ((α = .71) [21].Parents’ views and experiences of the care and information received during pregnancy, birth and postnatal period.Parents’ views and experiences of the *Growing Together* kit and its usefulness (intervention arm only).Respondents’ background characteristics will also be collected in all surveys and interviews.

### Sample size

The experience of motherhood questionnaire (EMQ), a 20-item self-report measure, has been used to determine the sample size [18] with the goal of reducing the proportion of women scoring low on the EMQ. A score of 40 on the EMQ is a typical median score for a sample of first time Australian mothers. We therefore expect 50% of women in the standard care to score 40 or less. To detect a difference of 10% (50% compared to 60%) scoring 40 or less between new mothers who have received the kit and those who have not would require 408 per group (total of 816 women) with 95% confidence and 80% power. Allowing for loss to follow up we therefore aim to recruit 1000 mothers. We do not anticipate needing to allow for any potential effect of clustering given we will ensure relatively equal numbers of women from the four geographically-based teams (i.e. the main factor which may introduce differences) will be allocated to both trial arms. Similarly, the clinical guidelines, models of care, and appointment length are all uniform across the four teams, thus minimising the potential for different influences based on team allocation. Where appropriate, we will adjust for demographic and birth outcomes.

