## Methods/design

We will undertake a two-arm cluster randomised controlled trial (RCT) to explore the impact of the *Growing Together* kit on women’s experience of motherhood and a range of parenting-related outcomes, and to compare these with the outcomes and experiences of women who received the usual hospital information (standard care). We will also explore parents’ views of the kit.

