### Randomisation and recruitment

The Women’s has four geographically-based maternity care teams, each of which has one antenatal clinic day per week (Monday - Thursday). To reduce the risk of contamination, (as would be the case if individual women were randomised), individual clinic booking days will be randomised, so that all women booking on a randomised day will receive the kit. Individual randomisation is not pragmatic given the high potential for clinician errors (clinicians would have to change the information they give to individual women throughout any booking clinic). Additionally, women may notice other women receiving different information packages.

Randomisation will be undertaken by an independent statistician at the Judith Lumley Centre. Using a blocked randomisation technique, the clinic days will be randomly allocated throughout the recruitment period to either intervention or standard care. The randomisation schedule will be kept confidential, with only the project coordinator, PhD student and senior research midwife having access in order to plan staffing for the research midwives.

As it is clusters (i.e. clinic days) being randomised and not individuals, randomisation will be done in advance, to ensure equal proportions of the four clinic days are randomly allocated to standard care and the intervention over the estimated 22 week recruitment period. The recruitment period was predicted based on the average number of booking visits per week at the Women’s and an estimation of women’s eligibility. For various reasons (e.g. geographical variations in the number of women meeting eligibility criteria), some clinic days may meet their quota of eligible women in fewer recruitment days than others. For this reason, recruitment will cease in each clinic (maternity care team) when their quota is reached.

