### Data management and analysis

Survey data will be entered into the REDCap data management system [27]. All data will be then transferred to Stata version 14 [28] for data cleaning and analysis.

Data accuracy will be checked through several steps, including verification of the missing data, the range and format of values and checking consistencies and frequency distributions. Any missing or inconsistent values will be checked with the hard copy surveys.

In relation to the trial outcomes, trial arms will be compared using intention to treat analysis. Randomising the various clinic days is likely to result in groups that are evenly distributed - however analyses of study outcomes will be adjusted for baseline differences between the groups as needed. The first stage of the analysis will describe the demographic characteristics in the two trial arms using numbers and percentages, and these data will enable us to understand what factors we need to take into account in the analysis of outcomes. Study outcomes will be compared using χ^2^ and relative risks, with an additional multivariate analysis where there are differences in demographic characteristics of the women in the two trial arms. Comparison of means will be undertaken for continuous variables using t-tests where data are normally distributed or medians compared otherwise using Mann-Whitney U tests.

If the proportions of missing data are above 5%, several steps will be considered to handle missing data. The missing values will be first explored by trial arm and based on the characteristics of the missing data to identify if missing data are missing completely at random (MCAR), missing at random (MAR) or missing not at random (MNAR). Multiple imputation will be conducted considering reasons for and amount of missing data, availability of predictors of missingness and variables that are correlated with the incomplete variable. If the proportions of missing data are very large (more than 40%), only the results of the complete case analysis will be reported and the interpretative limitations of the trial results will be mentioned [29].

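### Clinic days are randomised, but the sample size and the named tests treat women as independent, so the stated 80% power and 5% error are assured only if the day-level ICC is essentially zero

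*Protocol article*

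**What the plan says.** The section on randomisation and recruitment fixes the unit of allocation: "individual clinic booking days will be randomised, so that all women booking on a randomised day will receive the kit". It repeats the point when explaining the schedule: "As it is clusters (i.e. clinic days) being randomised and not individuals, randomisation will be done in advance". Each of the four teams has one clinic day a week, recruitment is expected to last 22 weeks, and allocation is blocked so that each team's days are split equally between arms.

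The Sample size section starts from the Experience of Motherhood Questionnaire (EMQ): "We therefore expect 50% of women in the standard care to score 40 or less". The target is "To detect a difference of 10% (50% compared to 60%) scoring 40 or less", which "would require 408 per group (total of 816 women) with 95% confidence and 80% power". Recruitment is set at 1000 to cover losses. On clustering it states: "We do not anticipate needing to allow for any potential effect of clustering given we will ensure relatively equal numbers of women". The support offered is that teams are balanced over the arms and that guidelines, care models and length of appointments do not differ between teams.

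The data management and analysis section compares outcomes with χ² and relative risks, adding a multivariate analysis where demographic characteristics differ. For scores: "Comparison of means will be undertaken for continuous variables using t-tests where data are normally distributed or medians compared otherwise using Mann-Whitney U tests". No method named there uses the clinic day or the team.

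**The concern.** The cluster is the day, but the argument for ignoring clustering is about teams. Allocating each team's days equally to both arms takes between-team differences out of the arm comparison. It leaves untouched whatever is shared by women who book on the same day. The section on implementation describes one possible source: the midwives running that day's booking visits hand over the kit, with a research midwife present to see that they know how. If delivery varies from day to day, that day's women share the variation.

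Where such correlation exists, a test that counts women as independent understates the variance of the arm difference. Intervals are then too narrow, the error rate exceeds 5%, and 816 analysed women carry less information than 816 independent ones. This would affect the primary EMQ comparison and every other comparison between arms. It is also a decision the article states, not a detail it leaves to a fuller document.

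**Working it through.** **Step 1: the plan's own figure.** Inputs from the Sample size section: p₁ = 0.50, p₂ = 0.60, 80% power, 95% confidence (taken as two-sided α = 0.05). With p̄ = 0.55 and d = 0.10:

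n₀ = [1.96·√(2·0.55·0.45) + 0.8416·√(0.50·0.50 + 0.60·0.40)]² / 0.10² = (1.379 + 0.589)² / 0.01 ≈ 387.3

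With continuity correction: n = (n₀/4)·[1 + √(1 + 4/(n₀d))]² = 407.1, rounded up to **408**. This matches the plan. The uncorrected formula gives 388 and a one-sided test gives 305. So 408 is the figure for independent women, with a design effect of exactly 1.

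**Step 2: cluster size.** 4 clinic days a week × 22 weeks = 88 days, about 44 per arm. Analysed women per day: m = 816/88 = 9.27. Recruited per day: 1000/88 = 11.4. The 88 is derived, not stated. Teams stop when they reach their quota, so day counts and sizes may differ, and unequal sizes would raise the design effect somewhat.

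**Step 3: effect of day-level correlation.** The documents give no ICC, so the range below is an assumption.

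- Design effect: DE = 1 + (m − 1)·ICC = 1 + 8.27·ICC
- Type I error of the unadjusted test: 2·[1 − Φ(1.96/√DE)]
- Power of a valid 5% test: the two-proportion formula at 408/DE per arm, with and without continuity correction

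| Assumed ICC | DE | Type I error, unadjusted test | Effective n per arm | Power, continuity-corrected | Power, uncorrected |
|---|---|---|---|---|---|
| 0 | 1.000 | 5.0% | 408 | 80.1% | 82.0% |
| 0.001 | 1.008 | 5.1% | 405 | 79.8% | 81.7% |
| 0.005 | 1.041 | 5.5% | 392 | 78.4% | 80.4% |
| 0.01 | 1.083 | 6.0% | 377 | 76.7% | 78.9% |
| 0.02 | 1.165 | 6.9% | 350 | 73.5% | 75.9% |
| 0.05 | 1.414 | 9.9% | 289 | 64.5% | 67.6% |

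Example at 0.02: DE = 1 + 8.27·0.02 = 1.165; 408/1.165 = 350; 1.96/√1.165 = 1.816, which gives 6.9%.

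**Step 4: the omitted team factor.** Team is balanced over arms but absent from the tests, so between-team variance inflates the estimated variance without entering the true one. The ratio of true to estimated variance is about 1 + (m − 1)·ICC_day − ICC_team. The test is anti-conservative unless ICC_team exceeds about 8.3 times ICC_day. Two assumed cases:

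- ICC_day 0.001, ICC_team 0.01: 1 + 0.008 − 0.010 = 0.998, so no inflation.
- ICC_day 0.02, ICC_team 0.02: 1 + 0.165 − 0.020 = 1.145, a type I error of about 6.7%.

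**The case against.** The strongest reply is that the day-level ICC may be very small. The primary outcome is an individual self-report scale taken at the 6-month interview, long after a single booking visit, in women who may have booked at any gestation up to 30 weeks. Kit hand-over is standardised, since kits are attached to histories beforehand. The article does not say that the staff of a clinic day differ from one week to the next. If each team's staff recur, midwife effects are largely team effects, and those are balanced. The relevant ICC is then what remains between days within a team, and nothing in the documents supports a value as high as 0.05. The analysis section also names χ² without a continuity correction; on that basis power is still 80.4% at an ICC of 0.005.

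Most of this stands, and it limits the size of the point. A reader might infer that the stated power and error rate definitely fail, or that any positive within-day correlation makes the p-values too small. The documents support neither. With no ICC given the loss cannot be fixed, and an omitted team effect can offset a very small day-level correlation.

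What does not stand is the article's own justification. Team balance says nothing about correlation within days, and no named test would detect or correct it. The offset is also weak: a day-level ICC of 0.01 would need a team ICC above about 0.08 (8.27 × 0.01) to cancel it, while the Sample size section itself argues that team differences are minimised.

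**Conclusion.** The point holds in conditional form. The arithmetic of 408 per group is correct for independent women, but women are not the units randomised, and the reason for ignoring clustering addresses the wrong level. The claimed power and the nominal 5% error are assured only if the day-within-team ICC is essentially zero or is offset by the omitted team effect. On the assumptions of 88 days, equal day sizes and ICCs from 0.001 to 0.05, the consequence runs from negligible (at or below 0.005: power within 2 points of 80%, error at most 5.5%) to material (from about 0.01: power 77% or less by the planned formula, error 6.0% or more). The analysis is the weightier half, because the choice of tests determines whether the reported p-values and intervals are valid. The power shortfall is modest unless the ICC is well above 0.01.

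**What to change.** 1. In the data management and analysis section, compare arms with a method that accounts for clinic day as the cluster. Cluster-robust variance, GEE, a mixed model or a cluster-level summary would each serve with about 88 days. Include maternity team as a fixed effect, since allocation is balanced on it, and report the estimated ICC.
2. In the Sample size section, remove the statement that clustering need not be allowed for, and restate the power at 408 per arm over a stated ICC range, saying which formula is used.

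The cost is a change of wording and a few lines of analysis code, as the clinic day is already the unit in the randomisation schedule. The downside is slightly wider intervals and a less favourable stated power. If the ICC proves to be near zero, the results will barely change. No extra enrolment is needed.

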The Growing Together book includes information about pregnancy and birth care options, different stages of the pregnancy and labour, care during pregnancy (including changing in the body and discomfort; relevant tests and screening; medicines, drugs and substances; important nutrients during pregnancy; when to contact hospital; emotional and mental health), labour and birth (e.g. preparing for labour and birth, when to go to hospital, pain relief in labour) and care after birth (e.g. breastfeeding; safe sleeping; sex and contraception; postnatal mental health).

Funding from the Victorian Government was granted to the Women’s to develop, and then distribute 2000 *Growing Together* kits and evaluate the outcomes. A team from Judith Lumley Centre (JLC) at La Trobe University in Melbourne, Australia, was engaged to undertake an evaluation of *Growing Together*, measuring various outcomes including women’s experience of motherhood, attachment, infant development, and parenting confidence as well as the views and experiences of health professionals.

This paper describes the study protocol for the kit evaluation.

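### The plan allows adjustment for birth outcomes, which follow allocation and may be affected by the kit, while the analysis section limits adjustment to baseline and demographic differences

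*Protocol article*

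**What the plan says.** Adjustment is described in two places in the protocol article.

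- **Sample size**, last sentence, after the discussion of clustering: "Where appropriate, we will adjust for demographic and birth outcomes".
- **Data management and analysis**: arms are compared by intention to treat, and "analyses of study outcomes will be adjusted for baseline differences between the groups as needed". Demographics are first described by arm, and "these data will enable us to understand what factors we need to take into account in the analysis of outcomes". Outcomes are compared by chi-squared tests and relative risks, "with an additional multivariate analysis where there are differences in demographic characteristics of the women in the two trial arms". Birth outcomes are not mentioned here.

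The timing comes from other sections. Women enter "at ≤30 weeks gestation at first pregnancy booking appointment" (Eligibility criteria and processes). Under Implementation of intervention, "On the intervention clinic days, all eligible women will receive the" kit at the first booking visit. Table 1 places the EMQ, the primary outcome, at the 6-month interview. The description of the kit says that its book deals with "preparing for labour and birth, when to go to hospital, pain relief in labour".

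The Study outcomes section adds that respondents' "background characteristics will also be collected in all surveys and interviews".

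**The concern.** Birth falls between receipt of the kit and measurement of the EMQ. A birth outcome is therefore a post-allocation variable, and the kit's content on labour and birth makes an effect on it plausible. Conditioning on such a variable has two consequences. If the kit improves the birth outcome and the birth outcome affects the EMQ, adjustment takes that part of the benefit out of the estimate. If an unmeasured cause affects both birth outcome and EMQ, adjustment also creates an association between arm and that cause which randomisation had removed. Either way, the adjusted figure no longer estimates the total effect promised by an intention-to-treat comparison.

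Nothing in the article labels the birth-outcome model as mediation, sensitivity or exploratory. If the condition in the Sample size sentence were applied as the demographic rule is, by looking for a difference between arms, adjustment would be triggered in exactly the situation where a kit effect on birth is most likely.

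A separate and lesser matter is that the remaining covariates are to be chosen after the arms have been compared, which leaves the choice to the analyst once data are seen.

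**Working it through.** **1. The plan's own figure.** Inputs from the Sample size section: 50% versus 60% scoring 40 or less, 95% confidence, 80% power, two equal groups. Two-sided testing is assumed.

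- Uncorrected: n = [1.96·√(2·0.55·0.45) + 0.8416·√(0.25 + 0.24)]² / 0.10² = (1.379 + 0.589)² / 0.01 ≈ 387.3, so 388 per group.
- With continuity correction: n' = (n/4)·[1 + √(1 + 4/(n·0.10))]² = (387.3/4)·(1 + 1.0504)² ≈ 407.1, so 408 per group, 816 in total.

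The stated 408 and 816 reproduce. The choice of adjustment covariates does not enter this calculation.

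**2. Order of events.** Booking and kit (30 weeks or less), then birth, then EMQ at 6 months. Birth outcomes are not baseline variables.

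**3. The two adjustment rules side by side.** Sample size: demographic variables and birth outcomes, where appropriate. Data management and analysis: baseline differences as needed, with an additional multivariate analysis if demographics differ. The second does not cover birth outcomes.

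**4. Part of the effect removed (assumed inputs).** The article gives no effect of the kit on any birth outcome, so a range is shown. On the risk-difference scale:

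adjusted difference = total difference − (kit's shift in birth outcome × birth outcome's shift in EMQ response)

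The total is set at the planned 10 percentage points.

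| Kit's shift in birth outcome | Outcome's shift in EMQ response: 5 points | 10 points | 20 points |
|---|---|---|---|
| 0 | 10.0 | 10.0 | 10.0 |
| 2 points | 9.9 | 9.8 | 9.6 |
| 5 points | 9.75 | 9.5 | 9.0 |
| 10 points | 9.5 | 9.0 | 8.0 |

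For example, 10 − 100·(0.05 × 0.20) = 9.0. Power of a two-proportion test without continuity correction at 408 per group is 82% for 10 points. It falls to 79%, 73% and 63% for 9.6, 9.0 and 8.0 points. These powers ignore any precision gained by adjustment.

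**5. Confounding opened (assumed inputs).** The true effect was set to zero, with an unmeasured binary cause in half of women. That cause raises an adverse birth outcome (20% without it in the control arm) and lowers EMQ response (from 60%), by 10 to 30 points each. In a simulation of 2,000,000 women per scenario, a kit shift of 5 or 10 points in the birth outcome gave adjusted estimates of about 0.0 to 1.0 percentage point. With no kit shift, the adjusted and unadjusted estimates agreed.

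The largest case can be checked by hand. Within arms, cov(birth, EMQ) = −0.30²·0.25 = −0.0225. The mean variance of the birth outcome is (0.35·0.65 + 0.45·0.55)/2 = 0.2375. The slope is −0.0225/0.2375 = −0.095, so the bias is 0.10 × 0.095 ≈ 0.0095, or about 1 point. The sign reverses if the kit lowers the adverse outcome.

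**6. Covariates chosen by imbalance.** A fixed rule (adjust only if a 5% test shows imbalance) was simulated with no true effect, 408 per arm, 8,000 trials and a standardised continuous outcome.

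| Covariate–outcome correlation | Mean estimate | Type I error | SD under rule | SD, always adjusted |
|---|---|---|---|---|
| 0 | 0.0002 | 4.65% | 0.0690 | 0.0691 |
| 0.3 | 0.0003 | 4.81% | 0.0689 | 0.0667 |
| 0.5 | −0.0008 | 4.42% | 0.0680 | 0.0610 |

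There is no bias. The cost is precision: at correlation 0.5 the variance is (0.0680/0.0610)² ≈ 1.24 times that of prespecified adjustment.

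**The case against.** The strongest reply is that the sentence is conditional and sits in the sample-size section, while the analysis section keeps the unadjusted chi-squared and relative-risk comparison and describes the multivariate analysis as additional. That stands. A reader might infer that the trial's main comparison is itself biased, but the document does not support this: only an adjusted estimate is exposed.

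It can also be said that the pathway may be weak. The Description of standard care section shows that the control booklet also prepares women for labour and birth, no birth outcome is listed among the study outcomes, and no kit effect on birth is quantified. This stands as a limit on size. It does not make birth outcomes baseline variables.

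Two further inferences go too far. One is that choosing covariates after looking at arm differences biases the estimate; under a fixed rule it does not (step 6). What remains is open discretion and lost precision. A full covariate list may properly be left to an analysis plan that is not shown.

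The other is that baseline covariates exist only for women who respond after birth. The Study outcomes section says that background characteristics are also collected in surveys and interviews, not that these are the only source. The Eligibility section describes screening from booking histories and referral sheets and a database of eligible women. For any covariate that is in fact taken from the surveys, an arm difference could reflect who responded.

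**Conclusion.** The point holds in a limited form. The Sample size section permits adjustment for variables that arise after allocation and that the kit could affect. This disagrees with the Data management and analysis section, and no label sets such a model apart from the effectiveness analysis. An estimate adjusted in this way would not be the total intention-to-treat effect.

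The size cannot be determined from the document. It is zero if the kit does not change birth outcomes. In the assumed range, a true 10-point difference is reduced by between 0.1 and 2.0 points through the pathway, and confounding by a shared cause moves a null effect by up to about 1 point. The upper ends need a large kit effect on birth, over and above a control booklet that also covers birth preparation.

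Choosing the other covariates by observed imbalance is a weaker choice than prespecifying them, mainly for precision and to limit discretion, and is not a demonstrated source of bias.

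**What to change.** Delete birth outcomes from the adjustment sentence in the Sample size section so that it agrees with Data management and analysis. If a model with birth outcomes is wanted, label it exploratory or mediation and report it apart from the effectiveness estimate.

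For the adjusted model, use a short set of pre-allocation covariates available from booking records, for example maternity team, maternal age and gestation at booking, and include them whatever the observed balance. Keep the unadjusted comparison as planned.

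The cost is one changed sentence and a small extraction from histories that are already opened at screening. The sample size stays at 408 per group.
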